### Blinding

Given the nature of the interventions it is not possible to blind patients or practitioners to treatment allocation. Although the cluster design of the trial might theoretically allow the researchers undertaking case note review to be blinded, our pilot study showed this was not possible in practice. The data analysis will be carried out by a statistician who is blind to treatment allocation.

### Sample size

Our estimation of sample size is based on the primary outcome of the number of healthcare contacts taking place in the four-week period following the index same-day consultation request. The estimation draws on a previous UK study comparing nurse-led telephone triage to standard practice for handling same-day consultation requests
[3]. That trial reported the number of NHS consultations based on general practice (GP and nurse), A&E and out-of-hours contacts. We believe this to be a good proxy for our primary outcome. Over the four-week follow-up of the trial the authors reported a mean number of NHS consultations of 1.02 (pooled SD 0.78) (Table four in
[3]) in usual care compared to a mean of 1.38 (pooled SD 1.79) in the nurse telephone-triage arm. Estimated trial sample size requirements for this trial are summarised in the table below. Four sample size scenarios are shown based on 80% or 90% statistical power and a intracluster correlation coefficient (ICC) of 0.01 or 0.05 (chosen as they represent the upper end of the average ICC reported from a survey across a range of outcome measures collected in trials from primary care settings
[46]) (see Table
1).

**Table 1 T1:** Sample size calculation

**Number per group***	**ICC**	**Design factor**	**Number of patients per group**	**Final number of patients per group+**	**Number of practices per group**
305*	0.01	3.26	994	1,867	4
305*	0.05	12.3	3,751	7,046	14
228^	0.01	3.26	743	1,396	3
228^	0.05	12.3	2,804	5,267	10

*At 90% power and 5% alpha; ^80% power and 5% alpha (both using the above means and SDs as per text); +after 6%
[3,27,28] of patients being excluded, 10%
[14,28,29] initially declining participation, 30%
[27-29] non-response to the request to return written consent to note review; of responders, 10% decline note review.

Selecting the most conservative sample size scenario (that is, 90% power, ICC 0.05) we estimate we require 3,751 patients per group to detect a difference of the magnitude reflected above (1.02 (0.78) versus 1.38 (1.79) primary care contacts in the follow-up period) in the primary outcome between the nurse-led triage and usual care arms. In order to inform the power study, and prior to undertaking the one-year pilot study (including the requirement for patient-written, rather than verbal consent), which would yield supporting data, we estimated that of all patients requesting a same-day consultation, 6%
[3,27,28] will be deemed ineligible, 10%
[14,28,29] will initially decline participation in the trial and/or follow-up of their notes, and 30%
[27-29] will not respond to the request to return written consent to note review. Of those who do respond in the questionnaire survey, we estimate 10% (conservative) will decline note review. Thus a total of 7,046 patients seeking same-ay consultations across 14 practices over a five-week period will be required in each of the three trial arms (see Figure
1). In the absence of a published effect size for the primary outcome for the GP-led triage arm, we estimated the sample size requirement on the claimed impact of a 30% reduction in GP workload with the Stour Triage system, and assumed a reduction of 30% in the primary outcome. At 90% power and an ICC of 0.05, a total of 1,983 patients in the GP-triage and usual management arms would be required. However, given the uncertainty of the estimate of a 30% reduction, we propose to recruit the same number of patients requesting same-day consultations as estimated for the nurse-triage arm, that is, 7,046 patients (and 42 practices).

The pilot study provided confirmation of our assumed ICC of 0.05 (that is, 0.03, 95% CI {AU query: CI ok as added?}0.00 to 0.08). Furthermore, the pilot study, led to a change in the method of patient consent to note review from written consent (obtained from completed patient questionnaires) to include verbal consent obtained from the treating clinician. The proportion of patients agreeing to case note review is anticipated to increase from an estimated 63% (original power study) to an estimated 78% under revised, and ethically approved consenting arrangements.

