**Methods/design:**

ESTEEM is a pragmatic, multi-centre cluster randomised clinical trial with patients randomised at practice level to usual care, computer decision-supported nurse triage, or GP-led triage. Following triage of 350–550 patients per practice we anticipate estimating and comparing total primary care workload (volume and time), the economic cost to the NHS, and patient experience of care, safety, and health status in the 4-week period following the index same-day consultation request across the three trial conditions.

We will recruit all patients seeking a non-emergency same-day appointment in primary care. Patients aged 12.0–15.9 years and temporary residents will be excluded from the study.

The primary outcome is the number of healthcare contacts taking place in the 4-week period following (and including) the index same-day consultation request. A range of secondary outcomes will be examined including patient flow, primary care NHS resource use, patients’ experience of care, safety, and health status.

The estimated sample size required is 3,751 patients (11,253 total) in each of the three trial conditions, to detect a mean difference of 0.36 consultations per patient in the four week follow-up period between either intervention group and usual care 90% power, 5% alpha, and an estimated intracluster correlation coefficient ICC of 0.05. The primary analysis will be based on the intention-to-treat principle and take the form of a random effects regression analysis taking account of the hierarchical nature of the study design. Statistical models will allow for adjustment for practice level minimisation variables and patient-level baseline covariates shown to differ at baseline.

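### Fourteen practices per arm cannot give the stated 90% power at ICC 0.05, however many patients are recruited; power for a difference of 0.36 is about 85%

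*Protocol article*

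**What the plan says.** The abstract (Methods/design) gives 3,751 patients in each arm "to detect a mean difference of 0.36 consultations per patient in the four week follow-up period", with "90% power, 5% alpha, and an estimated intracluster correlation coefficient ICC of 0.05". In the Sample size section, Table 1 builds this up in one row: 305 per group before clustering, ICC 0.05, design factor 12.3, 3,751 per group, 7,046 after allowing for exclusions and refusals, and 14 practices per group. The text adopts that row: "Selecting the most conservative sample size scenario (that is, 90% power, ICC 0.05) we estimate we require 3,751 patients per group". It then says that "a total of 7,046 patients seeking same-ay consultations across 14 practices over a five-week period will be required" in each arm. The Practice recruitment and Feasibility sections carry the same count as 42 practices in total.

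The cluster size behind the design factor is not printed. The section closes by reporting a pilot ICC of 0.03 (95% CI 0.00 to 0.08), introduced with "The pilot study provided confirmation of our assumed ICC of 0.05", and a rise in expected agreement to note review from 63% to 78%.

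**The concern.** In a cluster trial with a fixed number of practices, the number of practices limits the information once the ICC is appreciable. At ICC 0.05 each practice contributes at most 1/0.05 = 20 independent patients' worth, however many it enrols. Fourteen practices therefore supply fewer than the 305 that the plan requires before clustering. The design factor also appears to belong to a smaller practice contribution than the one the table implies.

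The 90% figure is the headline power for the primary outcome and supports the choice of 42 practices. If it is wrong, readers will credit the nurse-triage comparison with more power at the planning ICC than it has, and a null result could be over-read.

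**Working it through.** **Inputs** (Sample size section unless noted). Usual care mean 1.02, SD 0.78; nurse triage mean 1.38, SD 1.79; difference 0.36; 5% alpha, taken as two-sided; 90% power; ICC 0.05; 14 practices per arm. Retention is 0.94 × 0.90 × 0.70 × 0.90 = 0.533.

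**Reproducing the plan's figures**
- Variance sum: 0.78² + 1.79² = 3.8125.
- n per group = (1.96 + 1.2816)² × 3.8125 / 0.36² = 309 (plan: 305). The same formula at 80% power gives 231 (plan: 228). Both agree closely; a one-sided test would give 252 at 90%, so the plan's basis is two-sided.
- 305 × 12.3 = 3,751.
- 3,751 / 0.533 = 7,038 (plan: 7,046).

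**Ceiling with 14 practices**
- Effective n per arm = k·m / [1 + (m − 1)·ICC]. As m grows, this tends to k/ICC = 14/0.05 = 280, which is below 305.
- Fifteen practices also fall short: 15/0.05 = 300.
- Power at the ceiling: SE = √(3.8125/280) = 0.1167; Φ(0.36/0.1167 − 1.96) = 87.0%.

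**Cluster size within the row**
- Solving 1 + (m − 1)·ICC for m gives 227 from both printed factors: (12.3 − 1)/0.05 + 1 and (3.26 − 1)/0.01 + 1.
- 3,751/14 = 268. By the other route, 7,046/14 = 503 requests per practice, and 503 × 0.533 = 268.
- At 268 the factor is 1 + 267 × 0.05 = 14.35, and 305 × 14.35 = 4,377, not 3,751.
- At 227 per practice, 3,751 patients need 3,751/227 = 16.5 practices, not 14.

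**Power of the design as planned, ICC 0.05**
- Effective n = 3,751/14.35 = 261; SE = √(3.8125/261) = 0.121; power = Φ(0.36/0.121 − 1.96) = 84.6%. Scaling the SD so that the formula returns exactly 305 gives 85.1%.
- t reference with 2 × (14 − 1) = 26 df: 81.8%.
- Difference detectable with 90% power (normal): 3.2416 × 0.121 = 0.39.
- Largest ICC at which 0.36 has 90% power (normal): about 0.042.

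| Analysed per practice (14 practices, ICC 0.05) | Effective n | Power, normal |
|---|---|---|
| 227 | 258 | 84.2% |
| 268 | 261 | 84.6% |
| 332 (78% in place of the last two retention factors: 503 × 0.94 × 0.90 × 0.78, to rounding) | 265 | 85.1% |
| 393 (78% of all requests: 503 × 0.78) | 267 | 85.4% |
| Unlimited | 280 | 87.0% |

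**Other ICC values, 14 × 268, normal:** 96% at 0.03 and 67% at 0.08.

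**The 80% power, ICC 0.05 row** has the same fault: 10/0.05 = 200, below the 228 it requires.

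**The case against.** The strongest reply is that 0.05 was a deliberately cautious planning value. At the pilot estimate of 0.03 the same design has about 96% power, so the trial may well be adequately powered. That stands, and it limits the point: what is wrong is the claim made at 0.05. A reader might infer that the trial is underpowered outright or must recruit more practices. The documents do not support that, because 90% holds up to an ICC of about 0.042 and the pilot interval lies on both sides of that value.

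A reader might also infer that the 227 versus 268 mismatch is what puts 90% out of reach. It is not: 14 practices of 227 give 84.2%, and the limit comes from the number of practices alone. The mismatch is a separate inconsistency, and 227 is inferred from the two printed factors.

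A third tempting reading is that citing the pilot as support for 0.05 is a further error of arithmetic. It is only loose wording. The interval 0.00 to 0.08 contains 0.05, and six practices could hardly exclude 0.08.

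The Statistical analysis section adjusts for location, deprivation and list size, which could reduce between-practice variance. That may recover some power, but the sample size calculation takes no credit for it. Unequal practice contributions and the stated P-value adjustment for three comparisons act in the opposite direction. The documents do not let any of these be sized. The same section puts estimation ahead of testing, which softens the consequence but does not make the printed figure correct. Finally, this cannot be left to an unseen analysis plan, since the contradiction lies within a printed calculation.

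**Conclusion.** The point holds. At ICC 0.05, 14 practices per arm cannot reach 90% power for a difference of 0.36 at any recruitment. Planned power is about 85% on the normal basis that approximately reproduces the plan's 305, or about 82% on a t reference with 26 df. The revised consent arrangements move it only to about 85–86% (normal, allowing for either way of setting the SD). The Table 1 row is also internally inconsistent, at 227 against 268 per practice.

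The shortfall is about five points and applies to the nurse-triage versus usual care comparison at the planning ICC. It assumes unadjusted two-sided 5% alpha, equal practice contributions and no gain from covariates. It is an error in a stated figure that the trial relies on, and does not show that the design is inadequate at the ICC seen in the pilot.

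**What to change.** Keep 42 practices. In Table 1, recompute the design factor at the planned analysed cluster size (268, or the figure expected under 78% consent) and correct both ICC 0.05 rows so that the factor, patient number and practice count agree.

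Restate the claim in the abstract and the Sample size section on one named basis. On the normal basis, for example: with 14 practices of about 268 analysed patients per arm and ICC 0.05, power is about 85% for a difference of 0.36. Equivalent forms are 90% power for about 0.39, or 90% power for 0.36 only if the ICC is at most about 0.042. If a t reference is preferred, recompute all the figures on it, so that a t-based power is not paired with a normal-based ICC limit.

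As a secondary addition, give power at the pilot ICC of 0.03 (about 96%) and at its upper limit of 0.08 (about 67%), and describe the pilot as compatible with 0.05.

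The cost is a correction to text and table. Recruitment, data collection and analysis are unchanged; the stated power becomes somewhat less favourable.

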### Feasibility

An average practice (7,000 patients) accommodates around 714 consultations per week
[10] - approximately 142 consultations per day. Some
[4] have estimated that up to one-third of these are patients seeking same-day consultations; however, case definition is of importance, and we believe that an estimate of around 20 patients per day, 100 per week (14% of workload) clearly seeking same-day consultations is conservative, and reasonable; this was confirmed as realistic following our pilot and feasibility study. To achieve our sample size, we will need to recruit patients in 42 practices, each for a five-week period of patient recruitment. It is acknowledged, however, that practices vary in terms of the number of same-day consultation requests they receive (for instance due to practice size, nature of local population et cetera). To reduce the likelihood of this leading to significantly uneven patient recruitment across the different practices, in practices where the number of same-day consultation requests is significantly above the average, we will randomly sample sufficient numbers of patients from each practice to ensure proportionality across the practices.

For the patient-related outcomes, self-reported health status and perception of access to care will be collected by postal survey distributed from the patient’s registered GP using practice-headed notepaper, and with an estimated response rate after two reminders of 70%
[47-50]. The survey will be distributed four weeks following the index episode of care, to patients who have been identified for the trial. The survey response pack will incorporate written consent to review of the patient’s medical record with a view to capturing primary outcome measure data twelve weeks after the index episode of care. At 80% power and 5% alpha, our sample size of 7,046 per group will allow us to detect an effect size of 0.18 of a standard deviation at an ICC of 0.01 and an effect size of 0.34 of a standard deviation at an ICC of 0.05. Thus, we believe that the proposed sample size will allow us to be able to detect a small to moderate effect size in our patient-reported secondary outcomes.

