## Methods/design

### Design

The study is a pragmatic, three-arm, cluster RCT. Practices will be randomised 1:1:1 to receive GP-led triage, nurse-led computer based triage, or usual practice.

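### The detectable effects of 0.18 and 0.34 SD for the patient-reported outcomes do not follow from 7,046 per group; they match 7,046 taken as the total over three arms

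*Protocol article*

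**What the plan says.** The Feasibility section expects the four-week postal questionnaire to have an "estimated response rate after two reminders of 70" per cent. It then turns to the detectable differences for 80% power with a 5% alpha, and states that "our sample size of 7,046 per group will allow us to detect an effect size of 0.18 of a standard deviation" when the ICC is 0.01. For the larger ICC, the figure given is "an effect size of 0.34 of a standard deviation at an ICC of 0.05". From these two figures it concludes that a small to moderate effect on the patient-reported secondary outcomes can be detected.

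The Sample size section leaves no doubt about what 7,046 means. Table 1 lists it as the final number of patients per group, with 14 practices per group, in the row for 90% power and ICC 0.05 ("305* 0.05 12.3 3,751 7,046 14"). The text below the table repeats that "7,046 patients seeking same-ay consultations across 14 practices over a five-week period will be required in each of the three trial arms". Table 1 gives the design factors as 3.26 at ICC 0.01 and 12.3 at ICC 0.05.

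**The concern.** With 7,046 patients per arm, a detectable effect of 0.34 SD at ICC 0.05 looks too large, even after losing 30% to non-response. Both stated figures are high by a similar factor, which suggests a wrong sample size in the calculation rather than a rounding slip.

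These are the only precision figures the article gives for the patient-reported outcomes, and its conclusion about what can be detected rests on them. If they are too large, the plan understates its own sensitivity. A reader who uses them to judge a null result on patient experience or health status would treat that result as less informative than it is.

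**Working it through.** **Inputs**

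- 7,046 per group, 14 practices per group, design factors 3.26 and 12.3: Sample size section and Table 1.
- 80% power, 5% alpha, 70% response: Feasibility section. The section does not say whether alpha is two-sided; two-sided is assumed.
- Equal allocation to three arms: Design section.

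**Formula**

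For two equal groups of n analysed patients with design factor DE, the detectable difference in SD units is

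d = (1.96 + 0.8416) × √(2 × DE / n), with DE = 1 + (m − 1) × ICC for m patients per practice.

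**Step 1. Reproduce the stated pair.** Table 1's design factors are used throughout this step.

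| Patients per group in the calculation | n | d, ICC 0.01 | d, ICC 0.05 |
|---|---|---|---|
| 7,046, no loss | 7,046 | 0.085 | 0.166 |
| 7,046 × 0.70 | 4,932 | 0.102 | 0.198 |
| 7,046 / 2 × 0.70 | 2,466 | 0.144 | 0.280 |
| 7,046 / 3, no loss | 2,349 | 0.148 | 0.287 |
| 7,046 / 3 × 0.70 | 1,644 | **0.176** | **0.343** |

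Only the last row rounds to 0.18 and 0.34. It needs both steps: dividing by three and applying the 70% response. Solved backwards with the same design factors, the two rounded figures together need between 1,622 and 1,671 analysed patients per group, and 1,644 lies in that range.

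Other routes to the same pair exist, but each needs an input that departs from the stated basis: 90% power, one-sided or divided alpha, a different starting sample size, or a cluster size not given for this purpose.

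**Step 2. Check the design factor.** Table 1's factors imply m = (12.3 − 1)/0.05 + 1 = 227, and likewise (3.26 − 1)/0.01 + 1 = 227. The plan as written gives 7,046/14 = 503 patients per practice, and 503 × 0.70 = 352 expected questionnaires per practice. The design factors for the questionnaire outcomes should therefore be

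- ICC 0.01: 1 + 351 × 0.01 = 4.51
- ICC 0.05: 1 + 351 × 0.05 = 18.6

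**Step 3. Recompute with both inputs corrected.**

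| Basis | n per arm | m | d, ICC 0.01 | d, ICC 0.05 |
|---|---|---|---|---|
| 70% response | 4,932 | 352 | 0.120 | 0.243 |
| Also 6% ineligible and 10% declining: 7,046 × 0.94 × 0.90 × 0.70 | 4,173 | 298 | 0.122 | 0.244 |

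With a t reference on 26 degrees of freedom (28 practices in a two-arm comparison, minus 2), the multiplier rises from 2.80 to 2.056 + 0.856 = 2.91. The pairs become 0.125 and 0.253 (n = 4,932) and 0.127 and 0.254 (n = 4,173).

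**Step 4. Size of the error.** 0.18/0.120 = 1.50 and 0.34/0.243 = 1.40. At true effects of 0.18 and 0.34 SD, with 4,932 responders per arm and 352 per practice, power by the normal approximation is about 99% and 97%, not 80%.

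**The case against.** The strongest case on the other side is that little depends on these figures. The 7,046 and the 42 practices come from the primary outcome alone. The error is conservative, the claim of a small to moderate detectable effect survives at 0.12 to 0.24 SD, and no recruitment, consent or analysis step would change. The Statistical analysis section also puts estimation ahead of testing, so a null result should be read from its confidence interval rather than from a planning figure. All of this is fair. It limits the consequence but does not make the figures right.

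A second objection is that the replacement is less certain than a single pair suggests. Correcting only the per-group number and keeping Table 1's design factors gives 0.10 and 0.20. But those factors belong to 227 patients per practice, not the 352 questionnaires expected, so that pair would be too optimistic.

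The Statistical analysis section also mentions adjusting P-value cutoffs for the three comparisons without naming a method. If alpha were divided by three (an assumption), the results would be about 0.14 and 0.28, and the overstatement would shrink to roughly 20% to 30%. The sentence at issue states 5% alpha, however, and even the divided alpha does not reach 0.18 and 0.34.

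Finally, how the slip arose is an inference from matching numbers. The article does not show the calculation. The finding that the figures do not follow from their stated basis does not depend on it.

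**Conclusion.** The concern holds. At 80% power and two-sided 5% alpha, 7,046 per group cannot give detectable effects of 0.18 and 0.34 SD under the plan's own response rate and number of practices. The correct figures are about 0.12 SD at ICC 0.01 and 0.24 SD at ICC 0.05, or about 0.13 and 0.25 with a t reference on practices. The stated values are 40% to 50% too large.

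Two inputs are at fault and they act in opposite directions. The per-group number appears to have been divided by three, which inflates the effects. The design factor was taken at 227 per practice rather than at the questionnaires expected, which deflates them. The result rests on equal practice sizes, a 70% response and a common SD. The error affects the stated precision of the secondary outcomes only and leaves the sample size for the primary outcome as it is.

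**What to change.** In the Feasibility section, replace 0.18 and 0.34 SD with 0.12 and 0.24 SD (about 0.13 and 0.25 if a t reference on practices is used). State the basis alongside: about 4,200 to 4,900 responders per arm in 14 practices, with the design factor computed at the questionnaires expected per practice (about 300 to 350). If the adjustment for three comparisons is meant to apply to these outcomes, name the method and give the figures at that alpha as well. The cost is the correction of two numbers and one added sentence; nothing in the design, recruitment or analysis changes.
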